# Initial Statistical Analysis Plan

## **Analysis Plan**

### 1.1 Power and sample size

Assuming 5.3mmHg standard deviation of SBP (given variability of BP over time) and a two-sided significance level of 0.017 (to accommodate the three pairwise comparisons), our sample size of 60 in each intervention arm and 30 in the control arm provides 80% power to detect a difference in SBP reduction of 3.75 mmHg between either intervention and usual care, and a difference in SBP reduction of 3.1 mmHg between the remote monitoring and social influence arms. A preliminary data extraction shows about 2300 patients uncontrolled hypertensive patients in PFC, which should provide a sufficient population for enrollment.

### 1.2 Data analysis

As a randomized controlled trial, we will conduct intention to treat analysis. For patients with missing data, we will first include blood pressure readings from the EMR and then conduct multiple imputations.

The primary outcome will relate the systolic blood pressure during the 4 month visit to intervention arm, adjusting for the initial systolic blood pressure by including baseline measures in the model. For patients with missing data who do not complete the 4 month in-person blood pressure reading, we will conduct multiple imputation of the SBP values at 4 months as a function of baseline variables, including intervention arm.

Secondary analyses include modeling of normotensive status using logistic regression; estimation of recruitment and attrition rates; and evaluation of patient perceptions about the interventions from follow-up surveys. We will also compare medication adherence by intervention arm after enrollment. We will adjust these analyses for BMI, age, gender, race, forgetfulness (from the baseline and follow-up survey), and diabetic status. In addition, we will track BP measurements from the EMR that are obtained through usual care as well as during PCP visits, MPM messaging, phone calls; hospitalizations; and medication changes for up to 8 months after the study intervention using similar models. Lastly we will analyze diastolic blood pressure at the 4-month visit, adjusting for the initial diastolic blood pressure.

# Final Statistical Analysis Plan

**\*\*New changes from initial protocol notated in bold, parts removed from initial protocol notated in strikethrough**

## Analysis Plan

### 1.1 Power and sample size

Assuming 5.3mmHg standard deviation of SBP (given variability of BP over time) and a two-sided significance level of 0.017 (to accommodate the three pairwise comparisons), our sample size of 60 in each intervention arm and 30 in the control arm provides 80% power to detect a difference in SBP reduction of 3.75 mmHg between either intervention and usual care, and a difference in SBP reduction of 3.1 mmHg between the remote monitoring and social influence arms. A preliminary data extraction shows about 2300 patients uncontrolled hypertensive patients in PFC, which should provide a sufficient population for enrollment. **However, based on additional clinical information obtained after the study was initiated, we estimate a standard deviation for change in SBP of 20mmHg, larger than our initial estimate. Thus, we increased our accrual target to 100 in each intervention arm and 50 in the control arm, which provides 80% power to detect a difference in SBP reduction of 11mmHg between either intervention and usual care, and a difference in SBP reduction of 9mmHg between the remote monitoring and social influence arms.**

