## **Study Design**

### 1.1 Design

This is a prospective, randomized controlled trial: ~~150-250~~ patients will be randomized into one of three intervention arms: A) remote monitoring of blood pressure and medication adherence; B) remote monitoring of blood pressure and medication adherence with feedback to social support; and C) usual care. Participants will be randomized in a 2:2:1 ratio to the three study arms in variable blocks of 5 and 10 using a computer-generated randomization algorithm. The investigators will be blinded to the randomization assignment. The research coordinator and research assistants will be unblinded. The blind may be broken in the case of an emergency.

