### 1.2 Consent Process

We are requesting a waiver of the requirement to document consent and HIPAA authorization with a signature for participants enrolled into this study since we believe the research presents no more than minimal risk of harm to subjects and involves no procedures for which written consent is normally required outside of the research context. A majority of participants being enrolled in this study will be enrolled via a remote recruitment process, therefore we will read the IRB approved Consent/HIPAA script over the phone to each patient and ask them to provide verbal consent and verbal HIPAA authorization for use of their data in the study. Once a patient provides verbal consent, the research coordinator will select this option on the Consent/HIPAA screen on the participant dashboard that was just created for participation on the WTH health web platform for this study. At this point, the participant is randomized into 1 of the 3 study groups. After randomization, the coordinator will inform the participant of their assignment and read the instructions for their study group. A copy of the consent form will also be mailed to the participant's home address. A copy of the Consent/HIPAA document will also be included in the recruitment mailings sent to all patients before being called by the study team. While we do ask that

participants come for an in-person end of study visit, it is likely that due to attrition many will not complete the final visit. As is such, we believe it impracticable to collect the signed consent form at this time, as we will end up with an incomplete record of written consent. Therefore, a waiver of the requirement to document consent and HIPAA authorization with a signature is requested.

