### 1.2 Data analysis

As ~~is standard in~~ a randomized controlled trial, ~~we will conduct~~ **our primary analysis will follow the intention to treat approach, in which participants are analyzed according to their assigned treatment regardless of compliance.** For patients with missing **blood pressure** data, we will first include ~~blood pressure~~ readings available from the **electronic health record (EHR)** occurring from 90-150 days from the participant's start in the intervention, and then conduct multiple imputation **using all available baseline covariates.**

The primary ~~outcome analysis~~ will relate the systolic blood pressure ~~during~~ at the 4 month visit to **assigned** intervention arm, adjusting for the initial systolic blood pressure by including ~~the~~ baseline measures in the model. ~~For patients with missing data who do not complete the 4 month in person blood pressure reading, we will conduct multiple imputation of the SBP values at 4 months as a function of baseline variables, including intervention arm.~~

Secondary analyses include ~~modeling~~ **analyzing achievement** of normotensive status ~~by study arm~~ using logistic regression **and repeating the analyses for systolic blood pressure with diastolic blood pressure at the 4-month visit. We will estimate** ~~ion of~~ recruitment and attrition rates, and ~~evaluation of~~ patient perceptions about the interventions from follow-up surveys. We will also compare medication adherence **and blood pressure monitoring adherence** by intervention arm after enrollment. We will adjust these analyses for BMI, age, gender, race, forgetfulness (from the baseline and follow-up survey), and diabetic status. In addition, we will track BP measurements **by arm** from the (EHR) that are obtained through usual care **for up to 8 months after the study intervention. We will as well as during** ~~also evaluate~~ PCP visits, MPM messaging, phone calls, hospitalizations, and medication changes. ~~for up to 8 months after the~~

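### The flat 0.017 for three pairwise comparisons is valid but conservative; naming Shaffer's step-down in SAP 1.2 would raise per-comparison power from about 78% to 84% at the same 5% familywise error

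*Supplement*

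**What the plan says.** Section 1.1 (Power and sample size) of the final SAP uses "a two-sided significance level of 0.017 (to accommodate the three pairwise comparisons". The same figure stands in the final protocol under Statistical Considerations, Accrual and Analysis Plan. After the mid-study revision, "we estimate a standard deviation for change in SBP of 20mmHg", the target is "100 in each intervention arm and 50 in the control arm", said to give "80% power to detect a difference in SBP reduction of 11mmHg between either intervention and usual care" and the same power for "a difference in SBP reduction of 9mmHg between the remote monitoring and social influence arms". The final protocol's Design section agrees with those arm sizes: "Participants will be randomized in a 2:2:1 ratio to the three study arms".

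Section 1.2 (Data analysis) of the final SAP sets out an intention-to-treat analysis, "in which participants are analyzed according to their assigned treatment regardless of compliance". It adds substitution of health-record readings, multiple imputation and adjustment for baseline SBP. It names no significance threshold, no overall test and no step-down, closed or hierarchical procedure for the three contrasts.

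**The concern.** The three pairwise hypotheses of a three-arm trial are linked. If two of the pairwise nulls are true, the third must be true as well. So once one pair truly differs, at most one of the other two nulls can still be true, and after a correct first rejection only one false rejection remains possible. Holding all three tests at 0.017 guards against a case that cannot occur.

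What is at stake is efficiency. The stated objectives cover both the effect of monitoring and the added effect of social support, so more than one contrast matters. The detectable differences are already large, at 11 and 9 mmHg. Because section 1.2 is silent, a decision rule has to be written there in any case.

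**Working it through.** **Inputs (final SAP 1.1; allocation also in the protocol's Design section).** Arms A and B (interventions) 100 each, C (control) 50; SD 20 mmHg; alpha 0.017 two-sided per comparison; effects 11 mmHg (each intervention v control) and 9 mmHg (between interventions). The plan gives no dropout rate and no inflation, so loss is first set to 0.

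**Step 1. Reproduce the plan's power.** Power = Φ(Δ/SE − z), with SE = SD·√(1/n₁ + 1/n₂) and z(1 − 0.0085) = 2.387.
- Intervention v control: SE = 20·√(1/100 + 1/50) = 3.464; 11/3.464 = 3.175; Φ(3.175 − 2.387) = 78.5%.
- Between interventions: SE = 20·√(1/100 + 1/100) = 2.828; 9/2.828 = 3.182; Φ(3.182 − 2.387) = 78.7%.
- Differences giving exactly 80%: 3.464 × (2.387 + 0.842) = 11.2 and 2.828 × (2.387 + 0.842) = 9.1 mmHg, which round to the stated 11 and 9.
- At 0.05 they would be 3.464 × (1.960 + 0.842) = 9.7 and 2.828 × (1.960 + 0.842) = 7.9 mmHg. The revised figures therefore do rest on 0.017.

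**Step 2. Familywise error of Shaffer's step-down.** The number of true pairwise nulls can only be three, one or none.
- Three true: a false rejection needs the smallest p-value to be at or below 0.05/3. By Bonferroni the probability is at most 3 × 0.05/3 = 5%.
- One true: that null is never tested above 0.05, so the probability is at most 5%.
- None true: no false rejection is possible.

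**Step 3. Power.** Three independent arm means were simulated 1,000,000 times per scenario. The two control contrasts are correlated (1/50)/(1/100 + 1/50) = 2/3 through the shared control. Flat 0.017 is compared with Shaffer (0.05/3, then 0.05, 0.05). The first pair of columns uses the normal approximation and the second uses t tests with estimated variance.

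| Scenario and quantity | Flat, z | Shaffer, z | Flat, t | Shaffer, t |
|---|---|---|---|---|
| A and B both 11 better: each v control | 78.5% | 84.2% | 78.0% | 83.8% |
| Same: both v control (joint) | 68.9% | 80.5% | 68.2% | 80.1% |
| Same: at least one rejection | 88.1% | 87.9% | 87.7% | 87.6% |
| 11 and 20 better: A v B (9 mmHg) | 78.7% | 88.9% | 78.2% | 88.7% |
| 80/80/40, both 11 better: each v control | 67.6% | 74.3% | 66.7% | 73.6% |
| Same: both v control (joint) | 55.5% | 69.3% | 54.7% | 68.6% |

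The 80/80/40 rows assume 20% loss. That rate is an assumption, since the documents give none.

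**Step 4. Error check by simulation.** Global null, any rejection: 4.4% flat and 4.3–4.4% Shaffer. One true null with the third arm 11 or 30 mmHg apart: false rejection about 1.7% flat and at most about 5.0% Shaffer. No rejection made at 0.05/3 was lost under Shaffer in any replicate.

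**Step 5. Does the named procedure matter?** Yes. Plain Holm (0.05/3, 0.05/2, 0.05) does not use the link between the hypotheses. In the 11/11 case it reaches 74.0% joint power and 81.0% per control comparison.

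**The case against.** The best defence is that the plan contains no error. Bonferroni at 0.017 is valid and simple, its stated power reproduces, and it comes with matching 98.3% intervals, which have value in what the abstract calls a pilot trial. All of that stands, and it limits the point to a cheap improvement. Four stronger readings are tempting, and the documents do not support them.

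- *That the analysis is committed to flat 0.017.* The figure is a sizing alpha in section 1.1. Section 1.2 sets no threshold, so a sharper test at analysis is not excluded. It is only unspecified.
- *That the gain is the rise in joint power from 69% to about 80%.* The plan powers each comparison separately and never targets success of both interventions together. On its own scale the gain in the 11/11 case is about 6 points.
- *That the step-down restores the sensitivity lost when the SD went from 5.3 to 20.* The first rejection still needs 0.05/3, so the chance of finding any difference does not improve. If both true effects were 5 mmHg, that chance would stay at about 26% and per-comparison power would rise only from 17% to 21%.
- *That the step-down can never do worse than the plan's rule.* It keeps every rejection made at 0.05/3, but 0.017 is slightly larger than 0.05/3. A smallest p-value between 0.0167 and 0.017 would be lost. The effect is about 0.2 points or less in the cases above.

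The 84% and 89% also assume complete follow-up, whereas the protocol's Consent Process section expects that "it is likely that due to attrition many will not complete the final visit".

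**Conclusion.** The point holds as an inexpensive gain in efficiency. The flat rule is valid, and the documents show no inflated error and no wrong power figure.

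The size depends on the scenario. Per-comparison power rises by about 6 points when both interventions are 11 mmHg better than control. It rises by about 10 points for the contrast between interventions when they are 11 and 20 mmHg better. With an assumed 20% loss, the 11/11 gain is about 7 points, from about 67% to 74%. All of it arises after a first success.

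These figures rest on the plan's SD of 20 mmHg, equal variances, approximately normal arm means and the stated true effects. Adjustment for baseline, imputation and any unequal loss between arms are not modelled.

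**What to change.** In SAP 1.2, before any unblinded analysis, add a rule along these lines: the three pairwise p-values come from the baseline-adjusted primary model; the smallest is tested at 0.05/3; if it is rejected, the other two are tested in order, each at 0.05, stopping at the first non-rejection (Shaffer's procedure for three pairwise comparisons). Name the procedure explicitly, because a general reference to a step-down test could be read as Holm.

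Leave the 0.017-based sample size in section 1.1 and describe it as the conservative per-comparison figure. Report 98.3% intervals alongside 95% intervals, with a note that significance follows the step-down rule.

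The cost is a few sentences of SAP text and no extra participants. The real downside is that neither set of intervals matches the decisions one-to-one. For example, when the first step fails, a 95% interval may exclude zero for a comparison that is not declared significant.

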### 1.2 Data analysis

As ~~is standard in~~ a randomized controlled trial, ~~we will conduct~~ **our primary analysis will follow the intention to treat approach, in which participants are analyzed according to their assigned treatment regardless of compliance.** For patients with missing **blood pressure** data, we will first include ~~blood pressure~~ readings available from the **electronic health record (EHR)** occurring from 90-150 days from the participant's start in the intervention, and then conduct multiple imputation **using all available baseline covariates.**

The primary ~~outcome analysis~~ will relate the systolic blood pressure ~~during~~ at the 4 month visit to **assigned** intervention arm, adjusting for the initial systolic blood pressure by including ~~the~~ baseline measures in the model. ~~For patients with missing data who do not complete the 4 month in person blood pressure reading, we will conduct multiple imputation of the SBP values at 4 months as a function of baseline variables, including intervention arm.~~

Secondary analyses include ~~modeling~~ **analyzing achievement** of normotensive status ~~by study arm~~ using logistic regression **and repeating the analyses for systolic blood pressure with diastolic blood pressure at the 4-month visit. We will estimate** ~~ion of~~ recruitment and attrition rates, and ~~evaluation of~~ patient perceptions about the interventions from follow-up surveys. We will also compare medication adherence **and blood pressure monitoring adherence** by intervention arm after enrollment. We will adjust these analyses for BMI, age, gender, race, forgetfulness (from the baseline and follow-up survey), and diabetic status. In addition, we will track BP measurements **by arm** from the (EHR) that are obtained through usual care **for up to 8 months after the study intervention. We will as well as during** ~~also evaluate~~ PCP visits, MPM messaging, phone calls, hospitalizations, and medication changes. ~~for up to 8 months after the~~

~~study intervention using similar models. Lastly we will analyze diastolic blood pressure at the 4-month visit, adjusting for the initial diastolic blood pressure.~~ **We will repeat all analyses by subgroup related to time of enrollment (round 1 and round 2). Finally, we will perform a thematic evaluation of provider perceptions about the interventions from information gathered during follow-up telephone interviews as well as process data collected from a review of provider actions following monitoring encounters.**

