### 1.5 Primary Outcome Variable

The primary outcome is systolic blood pressure during the 4-month study visit by intervention arm, adjusting for the initial systolic blood pressure. For patients with missing data who do not complete the 4 month in-person blood pressure reading, we will conduct multiple imputation of the SBP values at 4 months as a function of baseline variables, including intervention arm.

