### 1.2 Data analysis

**As is standard in a randomized controlled trial, we will conduct our primary analysis will follow the intention to treat approach, in which participants are analyzed according to their assigned treatment regardless of compliance. analysis.** For patients with missing blood pressure data, we will first include blood pressure readings available from the electronic health record (EHR) occurring from 90-150 days from the participant's start in the intervention, and then conduct multiple imputation using all available baseline covariates.

The primary ~~outcome analysis~~ will relate the systolic blood pressure ~~during~~ at the 4 month visit to **assigned** intervention arm, adjusting for the initial systolic blood pressure by including **the** baseline measures in the model. ~~For patients with missing data who do not complete the 4 month in person blood pressure reading, we will conduct multiple imputation of the SBP values at 4 months as a function of baseline variables, including intervention arm.~~

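### The final SAP no longer names intervention arm in the imputation model for 4-month SBP, while the Final Protocol's primary-outcome section does; leaving arm out would pull the comparisons with usual care towards zero

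*Supplement*

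**What the plan says.** The Final Statistical Analysis Plan, 1.2 Data analysis, handles missing blood pressure in two steps. A health-record reading "occurring from 90-150 days from the participant's start in the intervention" is used first. What is still missing is then multiply imputed "using all available baseline covariates".

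The same section shows, struck out, a sentence that prescribed "multiple imputation of the SBP values at 4 months as a function of baseline variables, including intervention arm". By the document's own convention this is deleted text: "parts removed from initial protocol notated in strikethrough". The sentence is also struck in both data-analysis sections of the Final Protocol (Statistical Considerations 1.2 and Analysis Plan 1.2).

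The Final Protocol, 1.5 Primary Outcome Variable, carries the sentence as live text: "we will conduct multiple imputation of the SBP values at 4 months as a function of baseline variables, including intervention arm".

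The primary analysis model relates 4-month SBP to assigned arm, adjusted for baseline SBP.

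**The concern.** An imputation model should contain every term of the analysis model whose coefficient is to be estimated. Here that term is arm. If arm is left out, each missing value is drawn around a mean pooled over the three arms, so imputed participants carry little or none of their own arm's effect. Baseline covariates cannot make up for this: randomisation makes them independent of arm, so they hold no information on the treatment effect.

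Two analysts could each follow a current text and obtain different primary results. The Consent Process section expects many participants to miss the final visit, so the imputed share may not be trivial. The SAP also repeats the analysis for diastolic pressure and repeats all analyses by enrolment round, so the ambiguity carries through.

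**Working it through.** **The texts side by side**

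- Final Protocol 1.5: arm is named as a predictor.
- Final SAP 1.2 and Final Protocol Statistical Considerations 1.2: baseline covariates only; the sentence naming arm is struck.
- Final Protocol Analysis Plan 1.2: the same, although the strike there covers the whole primary-analysis paragraph.
- The SAP's sentence on the primary model mentions assigned arm and the baseline measures as separate things. That makes it more natural to read baseline covariates as not including arm.

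**The plan's own power figure**

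Inputs from SAP 1.1: 100, 100 and 50 participants, SD 20 mmHg, two-sided alpha 0.017, differences of 11 and 9 mmHg, power 80%. Power = Φ(δ/SE − 2.387), where 2.387 is the normal quantile for 0.017/2.

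- Intervention against usual care: SE = 20√(1/100 + 1/50) = 3.464; 11/3.464 − 2.387 = 0.788; power 78.5%.
- Between the intervention arms: SE = 20√(1/100 + 1/100) = 2.828; 9/2.828 − 2.387 = 0.795; power 78.7%.

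Both agree with 80% to within two points. There is no slack in the design for a shrunken estimate.

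**Expected bias if arm is omitted**

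Let m_j be the share imputed in arm j, μ_j the true arm mean and P the pooled mean of the observed values. Assume that within arm, missingness does not depend on the outcome. The expected mean in arm j is (1 − m_j)μ_j + m_j·P. With an equal share m, P cancels and every expected difference is (1 − m)δ.

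This was checked by simulating multiple imputation with Rubin's rules: 1,500 trials, 20 imputations, residual SD 20, a baseline covariate with slope 0.5, true difference 11 mmHg, alpha 0.017. The shares are assumptions.

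| Share imputed | (1−m)×11 | (1−m)×9 | Simulated, arm in | Simulated, arm out |
|---|---|---|---|---|
| 10% | 9.9 | 8.1 | 10.9 mmHg, power 72% | 9.7 mmHg, power 62% |
| 20% | 8.8 | 7.2 | 10.9 mmHg, power 67% | 8.6 mmHg, power 43% |
| 30% | 7.7 | 6.3 | 10.9 mmHg, power 58% | 7.6 mmHg, power 27% |

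The fall from about 80% to 72%, 67% and 58% is the cost of missing data and occurs either way. Only the gap between the last two columns belongs to this point.

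**Unequal shares**

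True means −11, −11, 0 and imputed shares 10%, 30%, 20% leave 90, 70 and 40 observed.

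- P = (90×(−11) + 70×(−11) + 40×0)/200 = −8.8.
- Remote monitoring: 0.9×(−11) + 0.1×(−8.8) = −10.78.
- Social support: 0.7×(−11) + 0.3×(−8.8) = −10.34.
- Usual care: 0.8×0 + 0.2×(−8.8) = −1.76.
- Differences from usual care: −9.02 and −8.58 in place of −11.
- Between the intervention arms: −0.44 in place of 0.

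With true means −11, −10, 0 and the same shares, a true −1.0 between the intervention arms becomes −1.21. With the two intervention shares exchanged (30%, 10%, 20%) it becomes −0.37. That contrast can move either way.

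With unequal shares, a difference from usual care is sure to shrink only when P lies between the two arm means, as it does in these examples.

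**The case against.** The strongest reply is that nothing in the current texts excludes arm. The struck sentence counted arm among the baseline variables, so a phrase covering all available baseline covariates may have been meant to include it. The edit also looks like de-duplication: the struck text described imputation twice in one section, and the final text keeps and expands one mention. The Final Protocol's outcome section gained the sentence naming arm, where the initial protocol's outcome section said nothing about imputation. On that view the passages are compatible. The mark-up is also uneven: the Final Protocol's Analysis Plan strikes even the primary model, and the SAP strikes phrases that another section shows as additions.

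This stands as far as intent goes. A reader might infer that the sponsor decided to drop arm; the documents do not show that. It does not settle what the SAP tells an analyst to do, since the one phrase that made arm's inclusion plain has gone from all three analysis sections.

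Two further inferences go too far. One is that every arm difference shrinks; the unequal-share example shows that a difference between the intervention arms can be created or enlarged. The other is that the bias follows the rate of missed visits; it follows only the share left after the health-record step, and the documents give neither figure.

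**Conclusion.** The point holds as a conflict between current texts on the primary outcome's imputation model, with the SAP's literal wording on the wrong side of it. It is not a proven decision to omit arm.

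If arm is omitted and the imputed share is equal across arms, the loss is about 1.1 mmHg on an 11 mmHg effect for each 10% imputed. In the simulation the added loss of power runs from about 10 points at 10% imputed to about 30 points at 30%. These sizes rest on an assumed share of 10% to 30%, missingness unrelated to outcome within arm, and a residual SD of 20 mmHg. With unequal shares, the comparisons with usual care still shrink when the two interventions have similar effects, and the contrast between the interventions may be biased in either direction.

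Because it concerns the primary analysis and the two readings can give materially different answers, it should be settled before the data are analysed.

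**What to change.** In the final SAP 1.2 and in both data-analysis sections of the Final Protocol, state that 4-month SBP still missing after the health-record step is multiply imputed from assigned arm, baseline SBP and all available baseline covariates, or separately within each arm. Keep the Final Protocol's 1.5 Primary Outcome Variable in line with this, and apply the same rule to diastolic pressure and normotensive status. Report the share imputed in each arm.

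The cost is one clause in three places. No data collection, sample size or patient procedure changes.
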